## **3. Study Design**

### **3.1. Design and Rationale**

This is a randomised, stratified between-groups study designed to assess the difference in saturated fat intake and coupon up-take between the three different experimental conditions; a) Planning and SMS reminders, b) Planning and c) Control Group. Subjects will be randomly allocated to one of these conditions and their responses will be measured by self-reported questionnaires.

Allocation to the subjects in the conditions will be stratified to balance by age group (30-45 years or 46-60 years), and gender. To help minimise any other imbalance effects obese (BMI $\geq$ 30) and non-obese participants (BMI $\geq$ 25), smokers and non-smokers will be also evenly allocated across the different cells.

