## **11. Statistical Considerations**

### **11.1 Description of Statistical methods and interim analysis**

This is a randomised, stratified, between-groups study with the factors 'Planning' and 'SMS Reminders'. The primary endpoint is the change in saturated fat and portion size changes in participants allocated to the three different experimental conditions (Planning, Planning and SMS Reminders and Control Group). Participants will be randomly allocated to one of these three conditions, stratifying for age group (30-45 years or 46-60 years) and gender. Self-reported portion size changes will be measured at a single point at the end of the study. Participants' saturated fat intake will be measured at baseline and upon completion of the study (2 weeks after enrolment). The statistical analysis will compare the efficacy of the three treatment groups via the change in saturated fat intake between the baseline and final diet assessments and change in portion sizes at the end of the study. There will be no interim analyses.

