### **11.2 Data Analysis and Plan of Efficacy**

A full statistical analysis plan will be formulated in collaboration with [name] from the Unilever Statistics Group, Colworth Park. The effect of the design factors will be determined by comparing the proportion of subjects who have reduced their self-perceived saturated fat intake. Analysis of variance with baseline covariates will be conducted to analyse the behavioural (TIS, FFQ, portion sizes changes, other health behaviours) and social-cognitive measures (intentions, self-efficacy, planning, feedback). Baseline self-reported saturated fat intake will be included as a covariate for the analysis of the primary outcome measures. The stratification variables will be included in the models as will other covariates found significant at the 0.05 level. Comparisons between treatments will all be reported using two-sided significance levels (i.e. making no prior assumption about which treatment group will be most effective). Separate analysis of the effects of modifiers and mediators will be conducted in order to gain a better insight as to who benefits from the intervention.

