### **11.3 Sample size and power determination**

The primary endpoint of self-perceived SAFA intake reduction will be assessed using analysis of variance with baseline covariates. Data from a previous study indicates that around 180 respondents should be sufficient to give power 0.8 of seeing a significant difference (at the two-sided 0.05 level) between the control and planning groups for this endpoint. No prior data exists for the portion size change measure.

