**RANDOMLY ASSIGN SMOKERS TO EACH CELL**

**Heart**

[Random/Multi]

Q8 Which, if any, of the following have you ever been diagnosed with?

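### Covariates beyond age group, gender and baseline intake enter the models only if significant at 0.05, so the primary model is partly data-chosen and BMI class and smoking have no assured place in it

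*Protocol*

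**What the plan says.** Section 11.2 specifies analysis of variance with baseline covariates for the behavioural and social-cognitive measures. For the primary outcomes one covariate is fixed: "Baseline self-reported saturated fat intake will be included as a covariate for the analysis of the primary outcome measures". The next sentence gives the rule for the rest: "The stratification variables will be included in the models as will other covariates found significant at the 0.05 level".

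Which variables count as stratification variables has to be read from other sections:

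- Section 3.1: "Allocation to the subjects in the conditions will be stratified to balance by age group (30-45 years or 46-60 years), and gender". It then adds obese and non-obese participants to a further balancing statement, and "smokers and non-smokers will be also evenly allocated across the different cells".
- Section 11.1 describes randomisation as "stratifying for age group (30-45 years or 46-60 years) and gender". It does not mention BMI class or smoking.
- Appendix 5, under the smoking question, instructs the recruiter: "RANDOMLY ASSIGN SMOKERS TO EACH CELL". The BMI question carries no such instruction.

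Section 11.3 ties the primary endpoint to the same type of model: "The primary endpoint of self-perceived SAFA intake reduction will be assessed using analysis of variance with baseline covariates".

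**The concern.** The rule lets the outcome data decide part of the primary model. The protocol does not list the candidate covariates. It does not say whether significance is judged once or separately for each outcome, or in which model. Two analysts could follow the sentence faithfully and report different adjusted treatment effects.

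BMI class and smoking are the sharper case. Section 3.1 sets out to balance them across the arms, but section 11.1 leaves them out of the strata, so they fall among the other covariates. When allocation balances a prognostic factor and the model omits it, the standard error is too large and the test is conservative. Whether that happens here would depend on a p-value.

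This is not a detail left to the statistical analysis plan. The protocol states the rule itself, and a plan written from it would inherit the rule.

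**Working it through.** **The plan's own figure.** Section 11.3 gives about 180 respondents for power 0.8, "at the two-sided 0.05 level) between the control and planning groups for this endpoint". It states no effect size or SD, so the figure cannot be reproduced. From d = (1.960 + 0.842) × √(2/n per arm), it corresponds to d = 0.295 if 180 is per group and d = 0.418 if it is the total (90 per group). Nothing below depends on it.

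**Inputs.** About 500 completers (section 6.2). Equal allocation is assumed, giving about 167 per arm and 334 in a two-arm comparison. The entry threshold is 0.05 (section 11.2).

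**1. Chance that an irrelevant covariate enters.** With k independent null candidates this is 1 − 0.95^k:

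| k | Chance that at least one enters |
|---|---|
| 2 | 9.8% |
| 5 | 22.6% |
| 10 | 40.1% |
| 20 | 64.2% |

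Ten is realistic. Appendix 5 records BMI, smoking, region, diabetes, blood pressure, perceived and measured cholesterol, a professional's report of high cholesterol, and family history. Appendix 3 adds Time 1 intentions, maintenance and recovery self-efficacy, and coping planning.

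**2. Chance that a truly prognostic factor enters.** By Fisher's z, this is Φ(atanh(r) × √(n − 3) − 1.96), where r is the partial correlation with the outcome:

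| r | n = 334 | n = 500 |
|---|---|---|
| 0.05 | 14.7% | 19.9% |
| 0.10 | 44.6% | 60.9% |
| 0.15 | 78.5% | 92.1% |
| 0.20 | 95.8% | 99.5% |

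Weak to moderate factors enter largely by chance; strong ones nearly always enter.

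**3. Effect on inference.** A two-arm analysis of covariance was simulated with n = 334, allocation blocked on BMI class and smoking, baseline as the fixed covariate, and eight null candidates. The assumptions, none from the protocol, are: half the sample obese, 20% smokers, residual SD 0.8, and a treatment effect of 0.25 for power. Age group and gender were left out for simplicity. BMI class and smoking, each scaled to unit variance, had a common coefficient β of 0, 0.1, 0.2 or 0.4. Their joint share of the variance left after baseline is 2β²/(2β² + 0.64), that is 0%, 3.0%, 11.1% or 33.3%.

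Type I error (4,000 runs; Monte Carlo SE √(0.05 × 0.95/4000) = 0.0034):

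| Joint share | Both always omitted | Both fixed | Selected at 0.05 | Best of 11 models |
|---|---|---|---|---|
| 0% | 0.058 | 0.058 | 0.059 | 0.067 |
| 3.0% | 0.045 | 0.047 | 0.048 | 0.056 |
| 11.1% | 0.033 | 0.046 | 0.046 | 0.050 |
| 33.3% | 0.015 | 0.048 | 0.049 | 0.051 |

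Power (2,000 runs):

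| Joint share | Both always omitted | Both fixed | Selected at 0.05 |
|---|---|---|---|
| 0% | 0.83 | 0.83 | 0.83 |
| 3.0% | 0.81 | 0.82 | 0.82 |
| 11.1% | 0.76 | 0.80 | 0.79 |
| 33.3% | 0.67 | 0.81 | 0.81 |

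A single selection step is nearly indistinguishable from the fixed model. Reporting the most favourable of 11 models raises type I error by at most 0.01 over the fixed model. The marked loss of power appears only when both factors are always omitted, which is not the protocol's rule.

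**The case against.** The strongest reply is that the rule protects itself. A factor that matters will be significant and so will be included. At n = 500, a factor with a partial R² of 5% (r = 0.224) enters about 99.9% of the time, and one with 2.5% (r = 0.158) about 94%. A factor that stays out has an observed partial R² below about 0.8%. Leaving it out moves the standard error by about 1/√(1 − 0.008) − 1 = 0.4%, or about 0.8% for two such factors. At n = 334 the corresponding figures are about 0.6% and 1.2%. This stands, and it rules out a claim of material precision loss.

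Three stronger readings are tempting, and the documents do not support them:

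- A reader might infer that the analysis disregards how subjects were allocated. It does not: both named strata are in every model, and baseline intake is in the primary ones.
- A reader might infer stepwise selection repeated for each outcome. The protocol says neither; it leaves the procedure open.
- A reader might take BMI class and smoking to be omitted design strata. Section 3.1 uses the term stratified only for age group and gender, and the smoking instruction in Appendix 5 can be read as ordinary randomisation. On the other hand, section 4.1 uses similar even-distribution language for gender and age group, which are strata. The status of the two factors is unsettled, and that is itself the defect.

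The reply does not supply a candidate list or a procedure, and the selection rule gains no power over a fixed list.

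**Conclusion.** The point holds in a limited form. The covariate set is partly chosen by the outcome data, may differ between outcomes, and does not guarantee adjustment for two factors that section 3.1 balances. That those factors enter only if significant is the plain reading of 11.1 and 11.2 together, not an explicit statement.

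The numerical effect is small: type I error within about 0.002 of the fixed model for a single selection step, at most 0.01 above it if the best of several models were reported, and power within about 0.01. These figures rest on the assumed prevalences, effect sizes and eight null candidates. They do not show that the reported p-values would be invalid.

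The case for change is pre-specification. For a self-reported primary outcome, the adjusted model should be known before the data are seen, and a better rule is available at almost no cost.

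**What to change.** Replace the selection rule in section 11.2 with a fixed set, for example:

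> Models include arm, age group, gender, BMI class (25–29.9 / ≥30), smoking status, and the baseline value of the outcome where one was measured. For portion size changes, a pre-named baseline saturated fat measure is used. No covariate is added to or removed from the primary model on the basis of its significance. A model with selected covariates may be reported as a sensitivity analysis.

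The words on where a baseline was measured are needed because, in Appendix 3, portion changes, action planning, feedback and general health behaviours are asked only at Stage 2. The baseline measure for portion size must be named because section 11.2 does not say whether baseline intake means the food frequency questionnaire or the two-item score.

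Reconcile sections 3.1 and 11.1 on whether BMI class and smoking are allocation factors, and make Appendix 5 agree.

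The cost is two degrees of freedom out of about 500. Appendix 5 already records BMI and smoking at screening, and no stated sample size, power or significance level changes.

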### **11.3 Sample size and power determination**

The primary endpoint of self-perceived SAFA intake reduction will be assessed using analysis of variance with baseline covariates. Data from a previous study indicates that around 180 respondents should be sufficient to give power 0.8 of seeing a significant difference (at the two-sided 0.05 level) between the control and planning groups for this endpoint. No prior data exists for the portion size change measure.

### **11.4 Definition of Data and Analysis Population**

Data will be recorded by subjects, captured via the on-line system and will be held in compliance with the UK Data Protection Act. Each subject will be identified by a unique ID number assigned to them.

The original data will be stored in the computer (but no hard-copies will be kept since this is an online study) and will be filed at Unilever for a minimum of five years from completion of the

study.

### **11.5 Responsibilities for Statistical Analysis**

All statistical analyses will be performed by the Unilever Statistics Group, Colworth Park

### **11.6 Reporting of deviations of statistical plan**

Any deviations of the statistical plan will be reported in the analysis.

### **Part III: General Considerations for Conducting a Protocol**

#### **1. Ethical Considerations**

##### **1.1 Declaration of Helsinki**

The current revision of the Declaration of Helsinki is the accepted basis for clinical study ethics, and must be fully followed and respected by all engaged in research on human beings. Any exceptions must be justified and stated in the protocol. Independent assurance that subjects are protected can only be provided by an ethics committee/institutional review board and freely obtained informed consent.

##### **1.2 Good Clinical Practice**

Good clinical practice is a standard for clinical studies, which encompasses the design, conduct, monitoring, termination, audit, analyses, reporting and documentation of the studies. It ensures the studies are ethically justified and scientifically sound, and that the clinical properties of the diagnostic/therapeutic/prophylactic product under investigation are properly documented. Refer to section 2.1.2 for further guidance.

## **2. Investigators Responsibilities**

It is the responsibility of the investigator(s) to conduct the study according to the protocol and to ensure that (s) he has the subject availability to conduct the study within the period defined in the study protocol.

### **2.1 Ethics**

#### **2.1.1 Declaration of Helsinki**

It is the responsibility of the investigator(s) to ensure that the study is conducted in full conformance with the principles of the current Revised Version (1989) of the Declaration of Helsinki.

#### **2.1.2 Good Clinical Practice**

It is the responsibility of the investigator(s) to ensure that the study is performed in accordance with Unilever's standards for the conduct of Human Trials and according to all local laws and regulations concerning Human studies. It is observed that due to the nature of Unilever human trials these do not qualify as Clinical Trials and as such, are not obliged by law to follow EU Directive 2001/20/EC (Clinical Trials Directive) or EU Directive 2005/28/EC (GCP Directive). However, Unilever Human Trials where possible operate to the spirit of these Directives in order to ensure best practice.

#### **2.1.3 Ethics Committee or Institutional Review Board**

It is the responsibility of the investigator(s) to submit a copy of the protocol and consent form to an ethics committee/institutional review board in order to obtain independent approval to conduct the study. Ethics committee/institutional review board approval must be obtained before the study is started. The approval of the ethics committee/institutional review board must be sent in writing, to the investigator(s). The Ethics Committee approval letter must mention the Ethics Committee members and their function.

#### **2.1.4 Informed Consent**

It is normally the responsibility of the investigator(s) to obtain informed consent from each subject participating in the study, after explanation of the aims, methods, benefits and potential hazards of the study. Since this study is solely conducted online the aims, benefits and potential harms to the subjects will be explained online (Appendix 2). The consent must and will be obtained before any study-specific procedures are performed.

It must be made completely and unambiguously clear to each subject that they are free to refuse to participate in the study, or that they can withdraw their consent at any time and for any reason, without incurring any penalty or withholding of treatment on the part of the investigator. The online action required for informed consent must be recorded and kept on file by the investigator(s).

#### **2.1.5 Withdrawal of a Subject**

N/A

### 2.1.6 Subject's Anonymity

The investigator(s) must ensure that the subject's anonymity will be maintained. On all documents, subjects must be identified only by an identification code and not by their names. To secure subjects' anonymity two third parties to Unilever will be involved. Virtual Surveys (online recruitment agency) will keep a separate confidential enrolment log that matches identifying codes with the subject's names and addresses. Tessella (IT development agency) will keep hold of subjects' mobile numbers to send the SMS Reminders and will delete the data upon completion of the study.

### 2.2 Protocol Amendment(s)

Any modification to the agreed protocol must be approved in writing by the sponsor/ study co-ordinator and the investigator(s). If alterations have to be made to the protocol after Ethical approval has been given, then the amendments will be submitted for their approval and not implemented until approval is received.

### 2.3 Case Report Form

N/A

### 2.4 Source Document Verification

N/A

### 2.5 Adverse Event

In the current study no treatment or direct intervention is offered and no medical tests are performed. Therefore, it is considered unlikely that subjects will experience adverse event as a result of participation in the study.

#### 2.5.1 Adverse Event Definition

Any untoward medical occurrence in a study subject or administered a treatment and which does not necessarily have to have a causal relationship with the treatment. An adverse event can therefore be any unfavourable and unintended sign (including an abnormal laboratory finding), symptom, or disease temporally associated with the use of a treatment, whether or not considered related to the treatment. Pre-existing conditions that worsen during a study are to be reported as adverse events. They can become Serious Adverse Events if they fulfil one of the seriousness criteria described below.

### SERIOUS ADVERSE EVENTS

Any adverse event that fulfils at least one of the following criteria:

- It is Fatal (results in death) (**note:** death is an outcome, not an event).
- It is Life-Threatening (**note:** the term "life-threatening" refers to an event in which the subject was at risk of death at the time of the event; it does not refer to an event which could hypothetically have caused death had it been more severe).
- It requires subject hospitalisation or prolongation of existing hospitalisation (**note:** "inpatient hospitalisation" refers to an unplanned, overnight hospitalisation).
- It results in persistent or significant disability/incapacity.
- It is a congenital abnormality/birth defect.
- It is medically significant or requires intervention to prevent one or other of the outcomes listed above.

Any adverse event that is considered SERIOUS must be reported. Since no treatment is offered to subjects and no medical tests conducted there is no such occurrence expected. Please see section

### 2.5.1

#### 2.5.2 Unexpected Adverse Treatment Reaction

An adverse reaction, the nature or severity of which is not consistent with the expected risks of participating in the study.

#### 2.5.3 Causality

Causality can be one of three possibilities:

- "NO" (definitely not treatment related)
- "YES" (remotely, possibly, probably or definitely treatment-related)
- "UNKNOWN"

All adverse events judged by either the investigator or the sponsor as being definitely not "NON TREATMENT-RELATED" qualify as Adverse Treatment Reactions.

#### 2.5.4 Adverse Event Severity - Definition

The severity/intensity of adverse events can be graded either on a three-point W.H.O. scale (*See W.H.O. Handbook for Reporting Results of Cancer Treatment*) e.g.

- **Mild** or *Grade 1*: discomfort noted, but no disruption to normal daily activities.
- **Moderate** or *Grade 2*: discomfort sufficient to reduce or affect normal daily activities.
- **Severe** or *Grade 3*: Inability to work or perform normal daily activities.

#### 2.5.5 Treatment and Follow-up of Adverse Events

N/A

### 2.6 Publication

Information relating to the study will be kept confidential and publications will be in a form with which the panellist cannot be identified.

### 2.7 Archiving

It is the responsibility of the investigator(s) to maintain adequate clinical study records. Copies of all clinical study material must be archived in the computer electronically (no hard-copies will be kept since this is an online study) for a minimum of five years from completion of the study (or more as legally required). All paper and electronic documents must be archived in a secure place and treated as confidential material.

### 2.8 Audit

The investigator agrees to comply with the sponsor and regulatory authority requirements regarding the auditing of the study.

## 3. Sponsor Responsibilities

### 3.1 General Responsibilities

The project manager/study co-ordinator, the investigator(s) and the study statistician will provide a final draft **protocol**. After mutual agreement, all parties sign the study protocol and submit the protocol to Ethics Committee.

The sponsor/study co-ordinator provides the investigator(s) with **sufficient material** and support

to permit the investigator(s) to conduct the study according to the agreed protocol. The sponsor/study co-ordinator reserves the rights to **terminate the study prematurely** for persistent protocol violations, or any other valid and ethical reasons. Should this be the case, the necessary procedures will be arranged after review and consultation by both parties to ensure protection of the subject's interests.

The sponsor provides treatment and/or **compensation** in the case of an injury to, or the death of, a subject, as a result of his/her participation in a study sponsored by them. The sponsor also **insures** the investigator(s) against, or indemnifies them for, losses resulting from liability for such injuries or deaths.

### **3.2 Monitoring and Contract Research Organisation Responsibilities**

N/A

### **3.3 Quality Assurance and Quality Control**

All material used in studies are subjected to **quality control**. Quality assurance audits may be performed by the sponsor or any health authority during the course of the study or at study completion.

### **3.4 Archives**

The protocol, approvals and all other essential documents related to the study must be archived, including certificates that satisfactory audit and inspection procedures have been carried out. All documents must be archived in a secure place for 5 years and treated as confidential material.

